### Trial design {8}

The study is a parallel two-group randomized controlled trial comparing motor timing performance of PD participants with and without music-based synchronous finger tapping training. In addition, data collected from a third arm, healthy controls, are assessed and serve as a normal, nonpathological baseline.

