### Outcomes {12}

The primary outcome measurements of this study are the following:
Improvement or preservation of SFT and continuous finger tapping (CFT) performances from baseline measurements for intervention group.Preserved or improved the Unified Parkinson’s Disease Rating Scale (UPDRS) scores from baselines measurements for intervention group in comparison to control arm.Reduced HbO_2_ levels in prefrontal cortex from baseline measurements for intervention group. Preserved or improved n-back task scores from baseline measurements for intervention group in comparison to control arm.Preserved or improved Montreal Cognitive Assessment (MoCA) scores from baseline measurements for intervention group in comparison to control arm.

Secondary outcome measurements of the study include:
Preserved motor control performances, UPDRS scores, HbO_2_ levels, n-back task scores and MoCA scores from baseline measurements in healthy control group.Preserved or aggravated motor control performances, UPDRS scores, HbO_2_ levels, n-back task scores, and MoCA scores from baseline measurements in PD control group.

These outcomes are determined by analyzing the differences between participants’ pre-, 4-week (during), 8-week (post), and 12-week (retention), neuroimaging, neurophysiological, and SFT performance scores as well as compared with the data from the control arms. Individual and grouped averaged measurements are examined.

Music-based therapies often report beneficial and positive results; however, little is known about how music improves neuronal activity and connectivity in individuals with neurological disease. The primary outcome measurements of this protocol: SFT and CFT performances, HbO2, UPDRS scores, n-back, and MoCA scores act as assessments to quantify the effects of a music-based synchronous finger tapping training in individuals with PD. The trial’s outcomes may be used to enhance current clinical care of patients with PD by supplementing or augmenting current PD treatments with music-based exercises. There are currently no anticipated harmful outcomes because the use of fNIRS has been shown to be clinically safe and feasible. Consequently, this study was determined to be a low-risk intervention by the participating hospital’s Ethics Committee and the Steering Committee.

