### Sample size {14}

For this study, a total 210 participants (70 participants in three groups with a 10% attrition rate), are recruited over an 18-month period. We aim to recruit an even distribution of age, PD staged I, and II as determined by the Hoehn and Yahr scale, and gender to maximize statistical significance. This study is an exploratory prospective randomized controlled study with the primary outcome being the HbO_2_ value measured by fNIRS. Because there are no pilot study nor previous studies identical to this, the sample size was calculated by using power calculations (where *α* = 0.05, *β* = 80%, and we assume a conservative average difference between the PD groups). Klempir et al.’s study was used to estimate the baseline averages of HbO_2_ changes; however, there are notable inherent differences between this protocol and the referenced study. Klempir et al. describes HbO_2_ changes between participants with and without DBS during a finger tapping exercise [34]. Although our study may involve participants who use DBS as a treatment, we are not examining how various forms of treatment (pharmaceutical or DBS) affect motor control. Thus, the estimated HbO_2_ baselines when DBS is ON from Klempir’s study were approximations of the PD control group’s performance.

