#### Finger tapping performances and neuropsychological assessments

The SFT and CFT performances as well as neuropsychological measurements collected from the three groups (intervention and control arms) during assessment will be compared using a two-sample *t* test. Correlative data and the extent of the intervention’s effect on finger tapping performances and PD symptoms may be extrapolated from this data.

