#### fNIRS data

An initial band pass filter will be applied to the raw fNIRS data before further processing to remove noise and drifts. Neuroactivity in various regions of interest including, prefrontal, pre-motor, supplementary, and primary cortex, will be analyzed by constructing a general linear model for each subject then estimating parameters and obtaining contrast values of the total oxy-Hb and deoxy-Hb signals. The contrast value images can be averaged within groups and a group analysis can be done using a *t* test. The averaged signal levels of each group will be plotted on a time vs total blood flow graph and compared to determine intervention effect.

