### Methods for additional analyses (e.g., subgroup analyses) {20b}

Further statistical analysis may be explored to account for interacting factors including gender, age, and different stages of PD as determined by the Hoehn and Yahr scale.

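### Two secondary outcomes are within-group claims of no change or no improvement from baseline, but the tests written for them are tests of difference, one of them between groups

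*Protocol article*

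**What the plan says.** Outcomes {12} sets two secondary outcomes, one for each group that does not receive the intervention. For healthy controls it is "Preserved motor control performances, UPDRS scores, HbO_2_ levels, n-back task scores and MoCA scores from baseline measurements in healthy control group". For PD controls it is "Preserved or aggravated motor control performances, UPDRS scores, HbO_2_ levels, n-back task scores, and MoCA scores from baseline measurements in PD control group". On how outcomes are judged, the section says "These outcomes are determined by analyzing the differences between participants" across the four visits and against the control arms, and that individual and group averages will be examined.

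The statistical methods section {20a} covers primary and secondary outcomes alike. Tapping and neuropsychological measures from the three groups "will be compared using a two-sample *t* test". For fNIRS, a linear model is fitted for each subject, contrasts are averaged within groups, and "a group analysis can be done using a *t* test"; the type of t test is not stated. Section {20b} adds only that "Further statistical analysis may be explored to account for interacting factors including gender, age, and different stages of PD".

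Trial design {8} explains the role of the healthy group: "healthy controls, are assessed and serve as a normal, nonpathological baseline".

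**The concern.** The outcomes and the tests, both written in this article, do not fit each other in three ways.

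- **Wrong contrast.** Both outcomes concern change over time inside one group. A two-sample t test across groups asks whether groups differ, so a healthy group that shifted and one that stayed still could give the same answer.
- **Wrong hypothesis.** *Preserved* is a claim of no material change. A t test takes zero difference as its null and can only fail to reject it. This also holds for the fNIRS t test, whichever type is used.
- **Hard to contradict.** *Preserved or aggravated* is not an equivalence aim. It allows no change and any worsening, so only improvement can count against it.

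With only difference tests written, a report could reach the word *preserved* through a non-significant p value. Tapping and the 3-back task are each done at four visits, so a practice effect is plausible. The rule in {20c} that removes missing and non-adherent data would make non-significance more likely, because it shrinks the sample.

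**Working it through.** **1. Outcome against test**

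| Secondary outcome | Claim | Test written | Does the test address it? |
|---|---|---|---|
| Healthy controls, tapping, UPDRS, n-back, MoCA | No change from baseline within the group | Two-sample t test between groups | No: wrong contrast and wrong null |
| Healthy controls, HbO2 | No change from baseline within the group | Group t test on contrasts, type not stated | At best it tests zero difference |
| PD controls, same measures | No improvement from baseline within the group | As above | As above, and only improvement contradicts the claim |

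**2. Inputs for a size**

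- Sample size {14} gives 210 participants, 70 per group (3 × 70 = 210), with 10% attrition. 70 × 0.9 = 63 completers per group. I assume the 70 is the number before attrition.
- The same section states "where *α* = 0.05, *β* = 80%, and we assume a conservative average difference between the PD groups". It gives no numerical difference or SD, so 210 cannot be reproduced from the article's own inputs. An assumed standardised difference of 0.5 (two-sided 5%, 80% power) gives 63 per group, then 63 / 0.9 = 70, and 210 in all. That is consistent with 63 completers but is a back-calculation.
- Sidedness is not given. I assume two-sided 5%.
- The correlation r between baseline and follow-up is not given. I assume 0.5, 0.7 and 0.8.
- The true change is expressed in baseline SD units, with equal SDs at both visits.

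**3. How often would a real change be non-significant?**

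I use a paired t test on change. The article does not write this test, but it is the one that fits the outcome, so the comparison is generous to the plan.

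SD of change = √(2(1 − r)). Non-centrality = (change / SD of change) × √n. The probability of non-significance is that a non-central t variable with n − 1 degrees of freedom lies within ±t(0.975, n − 1), which is ±1.999 for n = 63.

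True change 0.2 SD, n = 63:

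| r | SD of change | Non-centrality | P(non-significant) |
|---|---|---|---|
| 0.5 | 1.000 | 0.2000 × 7.937 = 1.587 | 65% |
| 0.7 | 0.775 | 0.2582 × 7.937 = 2.049 | 48% |
| 0.8 | 0.632 | 0.3162 × 7.937 = 2.510 | 30% |

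If all 70 complete, the figures are 62%, 43% and 26%. If removals left 40 (an assumption), the figure at r = 0.7 rises from 48% to 64%. A real shift of this size would therefore often go undetected, and more often as data are lost.

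**4. Would a margin rule solve it?**

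Only if the margin is justified on its own grounds. Take a rule that declares *preserved* when the 90% confidence interval for paired change lies inside ±0.4 SD, with n = 63 (simulated):

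| True change | r = 0.5 | r = 0.7 | r = 0.8 |
|---|---|---|---|
| 0 | 87% | 98% | over 99% |
| 0.2 SD | 47% | 65% | 80% |
| 0.4 SD (the margin) | 5% | 5% | 5% |

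The rule caps the error at 5% when the true change equals the margin. But at r = 0.7 or 0.8 it calls a true 0.2 SD change *preserved* more often (65%, 80%) than a paired test is non-significant (48%, 30%). A margin picked because 63 people can resolve it has no meaning of its own. It has to mark the change that would matter.

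**The case against.** The strongest reply has five parts.

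- **The misreading is not in the text.** A reader might infer that the plan will treat non-significance as stability. No sentence says so. Examining individual and group averages and plotting group signals also fits a descriptive reading. This stands, and the point is put only as a risk.
- **A margin or interval rule may sit in an analysis plan that is not shown.** This stands as regards the missing margin, and nothing here rests on it. It does not answer the mismatch, because the outcome and the test that do not fit are both in this article.
- **The healthy reference is not damaged.** A reader might infer that undetected drift in healthy controls spoils the benchmark. The Abstract compares the PD groups with the healthy group's baseline performance, and Eligibility criteria {10} says healthy controls supply baseline data. Drift at weeks 4 to 12 does not alter that reference. This largely stands.
- **The treatment effect is safe.** The PD arms are randomised and concurrent, so practice or signal drift common to both largely cancels, and the contrast does not need the control arm to be stable. This stands.
- **Two tempting figures do not hold.** Applying the two-sample test to baseline against a later visit makes a true 0.3 SD change non-significant 61% of the time and 0.2 SD 80%, but the article writes that test for groups, not visits. With no true change, *preserved or aggravated* escapes contradiction in 97.5% of two-sided 5% tests, but in that case *preserved* is the right answer, so this is not an error rate.

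**Conclusion.** The concern holds as a mismatch between stated outcomes and stated tests. Neither t test can establish *preserved*, the two-sample test does not address within-group change, and *preserved or aggravated* is contradicted only by improvement.

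If a non-significant result were taken as preservation, a true 0.2 SD change would pass 65%, 48% or 30% of the time at r = 0.5, 0.7 or 0.8, even with the better-suited paired test. This rests on 63 completers, a two-sided 5% level, and an SD scale and correlations that the article does not give.

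The impact is modest. These are secondary outcomes in two groups without the intervention, in a trial that calls itself exploratory. What is at stake is the wording of the secondary conclusions, not the randomised comparison.

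**What to change.** In Outcomes {12} and both parts of the statistical methods {20a}:

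1. Restate both secondary outcomes as mean within-person change from baseline to weeks 4, 8 and 12, with 95% confidence intervals, in either direction, for healthy controls and for PD controls.
2. Drop *preserved or aggravated* as an outcome.
3. State that a non-significant t test is not evidence of preservation.
4. If the word *preserved* is kept, declare it only when a 90% confidence interval for paired change lies wholly inside a margin. Justify the margin on clinical or measurement grounds and fix it before data lock. Do not choose it to suit the sample size.

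The cost is wording and a few intervals from data already to be collected, with no added participants or visits. The downside is that some measures will be reported as inconclusive.

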The use of fNIRS to assess neuronal response and its changes over time with music therapy as an intervention in patients with PD has not been explored yet. We take advantage of fNIRS’s high time resolution, locomotive freedom, and capabilities to detect neural activity in relevant motor control cortices as our primary quantitative measurement for investigating the neurophysiological effects and cortical neural activity changes from coupling motor movements with an external sensory cue. This protocol describes the implementation of an 8-week at-home finger tapping exercise while listening to a commonly known melody for participants with PD as a form of music therapy. In addition to fNIRS, various other assessments are used to determine and to track changes produced from the intervention over a 12-week period.

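### Outcomes {12} makes five domains primary while Sample size {14} makes HbO2 alone primary; the two must be reconciled into one between-arm outcome at one visit

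*Protocol article*

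**What the plan says.** Outcomes {12} opens with a list of primary outcomes: finger tapping (SFT and CFT), UPDRS, prefrontal HbO2, n-back and MoCA. It repeats the list at the end of the section: "The primary outcome measurements of this protocol: SFT and CFT performances, HbO2, UPDRS scores, n-back, and MoCA scores". On timing it says "These outcomes are determined by analyzing the differences between participants’ pre-, 4-week (during), 8-week (post), and 12-week (retention", and it singles out none of these visits.

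The items in the list are not worded alike. UPDRS, n-back and MoCA are each set against the control arm. Tapping and prefrontal HbO2 are described only as change from baseline in the intervention group.

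Sample size {14} describes an exploratory randomised study "with the primary outcome being the HbO_2_ value measured by fNIRS" and bases 70 participants per group on it. The Background agrees with that section: it takes fNIRS "as our primary quantitative measurement for investigating the neurophysiological effects".

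Statistical methods {20a} plans t tests for the tapping and neuropsychological measures and for the fNIRS contrasts. It does not say which comparison is primary.

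**The concern.** The two sections cannot both stand. One has a single primary outcome that fixes the sample size. The other has five domains of equal rank, four of which played no part in the power calculation. A later analysis plan that picked one outcome would have to override one of these sections, so this is not a detail left for that plan to fill in.

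What counts as the trial's answer is at stake. HbO2 could show no effect and the report could still lead with a favourable UPDRS, MoCA or tapping result at some visit, correctly calling it a primary outcome under Outcomes {12}. With several outcomes and three post-baseline visits, the chance that something favourable turns up by luck is well above the usual level.

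The wording of the HbO2 item adds a second problem. Read literally, the outcome that set the sample size is a before-after change in one arm. Randomisation does not protect such a change against practice, learning or time effects.

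**Working it through.** **1. The two sections side by side.**

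| | Outcomes {12} | Sample size {14} |
|---|---|---|
| Primary outcomes | Tapping (SFT, CFT), UPDRS, prefrontal HbO2, n-back, MoCA | HbO2 |
| Brain region for HbO2 | Prefrontal | Not stated |
| Visit | Weeks 4, 8 and 12, none primary | Not stated |
| HbO2 contrast | Intervention-group change from baseline | Difference between the PD groups |

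They differ on the number of primary outcomes and on the contrast for HbO2.

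**2. The stated sample size.** Inputs from Sample size {14}: alpha 0.05, a beta of 80% (read here as 80% power), 70 per group and 10% attrition. No difference or standard deviation is given, only that "we assume a conservative average difference between the PD groups". The figure therefore cannot be reproduced, but the standardised difference that it implies can be found. This assumes a two-sided test and that 70 is the number recruited.

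- Evaluable per arm: 70 × 0.9 = 63.
- d = √(2/63) × (1.960 + 0.842) = 0.499.
- Check with d = 0.5: n = 2 × (1.960 + 0.842)² / 0.5² = 62.8, so 63 per arm, and 63 / 0.9 = 70.

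The stated number fits one test at d of about 0.5. That d is back-solved and is not a protocol input.

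**3. Power if the five domains really were co-equal.** With a Bonferroni split and d = 0.499:

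| Tests | Alpha per test | Power at 63 per arm | Evaluable per arm for 80% | Recruited per arm |
|---|---|---|---|---|
| 1 | 0.05 | 80% | 63 | 70 |
| 5 (one visit) | 0.05/5 = 0.01 | 59% | 94 | 94/0.9 → 105 |
| 15 (5 × 3 visits) | 0.05/15 = 0.0033 | 45% | 115 | 115/0.9 → 128 |

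The stated size matches the single primary of Sample size {14}, not the list in Outcomes {12}.

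**4. Chance of a false positive if every listed primary were tested at two-sided 5%.** Assumptions, none stated in the protocol: no true effect; correlation 0 to 0.3 between outcomes and 0.5 to 0.7 between visits. The listed primaries are directional, so favourable results are counted first.

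- One visit, independent outcomes, favourable only: 1 − 0.975⁵ = 11.9%; 1 − 0.975⁶ = 14.1%.
- One visit, independent outcomes, either direction: 1 − 0.95⁵ = 22.6%; 1 − 0.95⁶ = 26.5%.
- The correlated cases were simulated with multivariate normal test statistics (400,000 draws).

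| | Favourable only (nominal 2.5%) | Either direction (nominal 5%) |
|---|---|---|
| 5–6 outcomes, one visit | about 10–14% | about 21–26% |
| 5–6 outcomes, three visits | about 21–32% | about 41–55% |

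**The case against.** **The trial is exploratory.** The Abstract and Sample size {14} both say so, and the Abstract sees the findings as informing larger studies. This softens the consequence. It does not say which outcome is primary, and the same document foresees clinical use: Outcomes {12} and the Discussion speak of enhancing current care, and Dissemination plans {31a} offers ward physicians directions on implementation.

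**Success on any test.** A reader might infer that the trial may declare success on any one of many 5% tests. The document does not say that. It states no success rule, gives alpha 0.05 only in the sample-size text, and could be read with HbO2 as decisive. What stands is narrower: nothing in the text prevents a positive report on another listed primary.

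**Multiplicity and visit may be in an analysis plan.** They may be, and their absence alone would be a weak point. The conflict between the two sections does not depend on that plan.

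**The control comparison is not wholly missing.** Outcomes {12} adds in general terms that data are also compared with the control arms, the last objective compares the two PD arms, and the sample-size text assumes a difference between them. So a between-arm contrast is probably intended. The HbO2 item still does not say so, while three neighbouring items do.

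**More regions and more tests.** A reader might see a further conflict in the fNIRS data section, which plans to analyse "Neuroactivity in various regions of interest including, prefrontal, pre-motor, supplementary, and primary cortex". There is none: analysing several regions is compatible with a prefrontal primary, and that section calls nothing primary. Nor do the documents support counting each tapping rate, region and haemoglobin signal as a primary test. The rates are stimulus settings, and the extra regions and deoxygenated signal are not listed as primary.

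**Conclusion.** The point holds as a contradiction within the protocol: five primary domains in Outcomes {12}, one in Sample size {14}. It is joined by an unnamed primary visit and by an HbO2 item that is not clearly a randomised contrast. This is wrong as written and should be corrected, because it determines which result answers the trial's question.

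The contradiction needs no assumption. The error rates do: they depend on testing every listed primary at two-sided 5% and on the correlations assumed, so they show the possible size and do not describe a stated plan. Stronger correlation between outcomes lowers them. The power figures rest on the back-solved difference of about 0.5.

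**What to change.** Amend Outcomes {12} to agree with Sample size {14}, and state the same in both sections:

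- One primary outcome: prefrontal HbO2, change from baseline, intervention versus PD control, at one pre-specified visit. Week 8, the end of training, is the natural choice. The documents do not dictate it, and the sponsor may justify another visit, but one must be fixed.
- Tapping, UPDRS, n-back, MoCA and HbO2 at the other visits become secondary. Either test them with a multiplicity adjustment (Holm would do) or report estimates with intervals and make no significance claims.
- Word every outcome that is meant as evidence of an intervention effect as a comparison with the PD control arm.

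The cost is that four domains lose primary status. No new data are needed, and 70 per group can stand on this account. The protocol and registry entry should be changed together, ideally before recruitment and in any case before analysis, which the protocol starts only after the last 12-week assessment. If the sponsor prefers to keep all five domains as primary, the sample size has to be recalculated for that and the success rule stated.

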### Participant timeline {13}

Figure 1 graphically shows the participant timeline. Figure 2 illustrates the standard protocol.

